**10. Outcomes**

**10.1 Primary outcome**

The secondary efficacy outcomes include the percentage decrease in the average duration of seizures after surgery compared with before, improvement in the severity of epilepsy after surgery, frequency of epileptiform discharge by 24h video EEG, evaluation of postoperative quality of life, improvement in migraine in patients with migraine complications, headache impact test, incidence rate of adverse events, cardiac ultrasound index, and some laboratory indicators.

The primary efficacy outcome of our trial is the percentage reduction in the frequency of epileptic seizures during the first year after surgery compared to before surgery. The seizures must conform to the description of seizure characteristics in the International League Against Epilepsy (ILAE), and the preoperative seizure frequency is measured in months and calculated based on valid seizure diaries only. The postoperative seizure frequency is calculated in the same way but should ensure that patients have valid seizure diaries for over 95% of the entire follow-up period.

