**5.2 Participants Eligibility**

Participants included not only patients but also the staff of the research team. For patients, we set a series of inclusion and exclusion criteria, which could seen in Supplement file 3, and for practitioners, we also set recruitment conditions and training procedures.

Inclusion criteria

1.It conforms to the diagnostic criteria for epilepsy by the International League Against Epilepsy, i.e., ILAE (2014 version).

2.It conforms to the diagnostic criteria for refractory epilepsy by the ILAE (2010 version).

3.It conforms to the diagnostic criteria for PFO by the American Society of Echocardiography (ASE) and Society for Cardiac Angiography and Intervention (SCAI) (2015 version). Participants are required to have a second or higher grade of RLS, detected using transthoracic echocardiography with contrast injection, as shown in Figure 4 [2].

4.Patients aged 18 to 55 years-old, who can complete the epilepsy diary independently or with the help of family members.

5.Participants should have at least one epileptic seizure observed during the 6-week recruitment screening period and confirmed by a 24-hour video electroencephalogram (EEG) immediately after the seizure.

6.Participants are required to maintain a stable antiepileptic medical therapy during the screening period and throughout the trial, and to keep their medication regimen as unchanged as possible without an emergency event.

7.Participants were required to have a valid documented epilepsy diary for at least 4 weeks during the recruitment screening period.

8.Participants should agree to participate in this trial and sign an informed consent.

Exclusion criteria

1.Participants with history of pseudo-seizure.

2.Participants with serious mental illness, such as anxiety or depression.

3.Participants with cognitive dysfunction (Mini-Mental State Examination score ≤ 23).

4.Participants with vascular puncture site infection or difficult puncture.

5.Participants with PFO associated with other cardiac structural abnormalities, such as moderate or higher valvular regurgitation and pulmonary hypertension.

6.Participants who have contraindications for antiplatelet therapy such as open trauma fracture surgery, gastrointestinal ulcers, active bleeding, and visceral bleeding three months before the screening period.

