**11. Sample size calculation**

Prior to this study, we recruited 28 subjects with refractory epilepsy to undergo PFO closure surgery and followed them up for one year after the operation. The primary efficacy outcome of this trial is the percentage decrease in the frequency of epileptic seizures during the first year after surgery compared to before surgery. In the 28 patients, the mean percentage decrease was 49.60%, with a standard deviation of 41.67%.

Combined with the control group parameter settings in drug research on refractory epilepsy treatment, we estimate that the surgical group's average therapeutic effect in this study is 50%, with a standard deviation of 0.42. The average percentage decrease in the control group, based on previous literature, is set at 20%, with a standard deviation of 0.20. Therefore, with a superiority margin of 0.1, a single-sided alpha of 0.025, and a test power of 0.80, the total sample size required is 88. To account for possible subject withdrawal and loss of follow-up, we increase the sample size required by 20%. Therefore, we plan to recruit approximately 110 subjects for this study.

12. **Statistical analysis**

1.Program of analysis set

The complete analysis plan consists of three sets: Full Analysis Set (FAS), Per-Protocol Analysis Set (PPS), and Safety Set (SS). Both FAS and SS will include all participants who are randomly assigned, but those with serious protocol violations, active withdrawal, serious adverse events, or extremely poor compliance will be excluded from PPS. For FAS, we intend to follow the modified intention-to-treat (mITT) analysis principles, which will exclude participants without a PFO diagnosis confirmed by intracardiac echocardiography during the surgical procedure.

2.Missing data

In the event that patients are lost to follow-up during the study, their corresponding data will be carried over and included in the analysis. The evaluation process will be performed by the project team's doctors, and the data will be reviewed by the data monitoring committee.

3.Statistical analysis methods

The demographic characteristics of PRE receiving PFO closure and those not receiving it will be compared to assess bias and ensure accurate representation of the participants. Primary and secondary outcomes will be described statistically using mean ± standard deviation, median, minimum, maximum, and other indicators. Categorical data will be described using frequencies and percentages.

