The primary outcome of the trial will be analyzed using a mixed model of fixed and random effects, and factors with significant differences between the baseline datasets will be incorporated into the model as control variables. Additional analyses will include t-tests, chi-square tests, rank-sum tests, logistic regression, and propensity score matching to examine the secondary outcome indicators. Covariance analysis and mixed-effects models that consider the effect of time will be used to examine temporal trends in the clinical characteristics of epilepsy. All analyses will be performed using R-project version 4.2.1. Statistical significance will be set at two-sided p<0.05.

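### Comparing arm means of a per-patient percentage reduction, with no floor and a denominator that may be one seizure, is less efficient than a baseline-adjusted log-rate or rank analysis of the same diaries

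*Protocol*

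**What the plan says.** Protocol section 10.1: "The primary efficacy outcome of our trial is the percentage reduction in the frequency of epileptic seizures", taken over the first postoperative year relative to the period before surgery. On the denominator it adds that "the preoperative seizure frequency is measured in months and calculated based on valid seizure diaries only".

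Section 5.2 sets how little that denominator may contain. Inclusion criterion 5 reads: "Participants should have at least one epileptic seizure observed during the 6-week recruitment screening period". Criterion 7 reads: "Participants were required to have a valid documented epilepsy diary for at least 4 weeks during the recruitment screening period". Follow-up lasts 48 weeks (section 5.1).

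Section 11 works with the mean and standard deviation of the percentage. In the 28 pilot patients, "the mean percentage decrease was 49.60%, with a standard deviation of 41.67" per cent. The planning values are 50% (SD 0.42) with closure and 20% (SD 0.20) in control, with a margin of 0.1.

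Section 12 says: "The primary outcome of the trial will be analyzed using a mixed model of fixed and random effects". Covariates enter only if they differ significantly between the arms at baseline. Rank-sum tests appear only among the methods for secondary outcomes. No floor, transformation, count model or higher seizure minimum is stated.

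**The concern.** A ratio with a small random count in its denominator is a fragile thing to average. Improvement is capped at +100%, but deterioration, or merely a quiet screening month, can produce a score of several hundred per cent below zero. The noisier of the two diary periods is the divisor: 4 to 6 weeks against 48.

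What is at stake is mainly power and readability. If a small part of each arm supplies most of the variance, the comparison of means uses the diary data inefficiently, and the reported arm means may say little about the typical patient. Baseline seizure rate, the obvious covariate, is adjusted for only if it happens to differ between the arms.

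**Working it through.** **1. The plan's own sample size.** Inputs from section 11: SDs 0.42 and 0.20, means 50% and 20%, margin 0.1, one-sided alpha 0.025, power 0.80.

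n per arm = (0.42² + 0.20²)(1.960 + 0.842)² / (0.30 - 0.10)² = 0.2164 × 7.851 / 0.04 = 42.5

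This gives 43 per arm (86). The noncentral-t version gives 44 per arm (88), and 88 / (1 - 0.20) = 110. The stated figures reproduce. The issue is the scale of the outcome, not this calculation.

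**2. How the score behaves.** Score = 1 - (follow-up rate / baseline rate).

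- One seizure in a 4-week baseline, then 36 in 48 weeks (3 per 4 weeks): 1 - 3/1 = -200%. This offsets four patients at +50%, since -200 + 4 × 50 = 0. With three baseline seizures and the same follow-up, the score is 0%.
- One seizure in 4 weeks, then 6 per 4 weeks: 1 - 6/1 = -500%. Compared with a patient at the expected 20%, the mean of an arm of 44 moves by (-5.00 - 0.20)/44 = -0.118, about 12 points. The margin is 10 points.

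**3. Power by scale.** The protocol gives no seizure-rate distribution, so everything here except the design is assumed. Set-up: 44 per arm, at least one baseline seizure, 48 weeks of follow-up, underlying rate reductions of 20% and 50%, lognormal patient rates. The tests are unadjusted and against zero, one-sided 0.025. Clustered means gamma variance 0.5 per 4 weeks (shape 2).

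| Median per 4 wk | Log SD | Baseline | Counts | Arm means | t-test on percentage | Rank test | t-test on log rate ratio |
|---|---|---|---|---|---|---|---|
| 1 | 0.5 | 4 wk | Poisson | 33%, 58% | 0.91 | 0.92 | 0.95 |
| 2 | 1.0 | 6 wk | Poisson | 9%, 43% | 0.90 | 0.97 | 0.97 |
| 8 | 1.0 | 6 wk | Poisson | 10%, 44% | 0.98 | 1.00 | 1.00 |
| 15 | 1.0 | 6 wk | Poisson | 14%, 46% | 0.99 | 1.00 | 1.00 |
| 2 | 1.0 | 4 wk | Clustered | -3%, 36% | 0.56 | 0.73 | 0.77 |
| 4 | 1.0 | 4 wk | Clustered | -25%, 22% | 0.49 | 0.72 | 0.79 |
| 8 | 1.0 | 4 wk | Clustered | -43%, 10% | 0.47 | 0.73 | 0.79 |

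The clustered rows also have the shorter baseline, so the two blocks differ in more than clustering. Step 4 holds the baseline at 6 weeks.

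Across all settings run, the 5% of patients furthest from the mean carried 43-87% of the variance. In nine settings examined further, control patients with one or two baseline seizures made up 3-80% of the arm and carried 51-88% of its variance. Removing the two lowest of 44 controls moved the arm mean by a median of 4 to 23 points.

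**4. Baseline-adjusted alternatives.** With a 6-week baseline and medians from 0.5 to 15 per 4 weeks, a log-rate or rank ANCOVA was at least as powerful as the comparison of mean percentages in all 18 settings: 0.80-1.00 against 0.77-1.00 under Poisson counts, and 0.73-0.96 against 0.56-0.68 under shape-2 clustering.

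**5. Direction of the arm means.** Poisson counts, log SD 0.8, 6-week baseline, underlying reductions 20% and 50% (difference 30 points):

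- Median 0.5 per 4 weeks: arm means 36% and 60%, difference 24 points.
- Medians 1.5 to 6 per 4 weeks: arm means about 5-10% and 40-44%, difference 34-36 points.

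The one-seizure entry rule pushes the means up when rates are low. The random denominator pushes them down otherwise.

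**The case against.** **The pilot looks mild.** With 28 patients, mean 49.60 and SD 41.67, no patient can lie below 49.60 - (27/√28) × 41.67 = -163%, so even the -200% example could not have occurred there. In the shape-2 scenarios (medians 1.5-6, log SD 0.8, 6-week baseline) the closure SD is 66-119 points, and a sample of 28 would show an SD of 41.67 or less only 3-17% of the time. The Poisson settings, where the loss is small, fit better. This stands as a reason for caution about size. It does not settle the matter: the pilot had no control arm and its baseline length is not given.

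**Part of the gap is adjustment, not scale.** Under shape 2, an unadjusted log-ratio test reaches 0.71-0.73 against 0.85-0.93 for the log ANCOVA, and adjusting the percentage for log baseline lifts it from 0.44-0.61 to 0.61-0.70. This stands, and it is why the covariate is the first part of the fix.

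**Power was compared against zero.** The protocol has no margin on a ratio scale to test against. With the 0.1 margin, the mean-percentage test has power 0.49-0.96 in the tabulated Poisson rows and 0.30-0.32 in the clustered rows, with no log-scale counterpart.

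**The model may be settled in the SAP.** Section 12 names a mixed model without a distribution or link, so a normal-theory analysis is inferred from the sizing. But the outcome scale, baseline window, one-seizure minimum, margin and sizing on means are fixed in the protocol. An SAP that moved to log rates would no longer match section 11.

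**Stronger readings that the documents do not support.** A reader might infer that the arm means are always too low and the difference overstated. Step 5 shows both directions, and the protocol states no underlying-rate target: its 50% is based on the pilot's observed mean of the same percentage. A reader might also infer that only a few patients are influential, but they may be most of the arm. Nor is every baseline count guaranteed to be at least one: the qualifying seizure may fall outside the valid diary days.

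**Conclusion.** The concern holds as a loss of efficiency and interpretability. A per-patient percentage compared by means lets low-baseline patients carry much of the variance, and a baseline-adjusted log-rate or rank analysis uses the same diaries better. The loss is small for high, Poisson-like seizure rates and large when seizures cluster in time. Which applies depends on rates and clustering that the protocol does not give. That the score is per patient is inferred from the mean and SD in section 11.

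Arm means may differ from the underlying rate reduction in either direction. No fixed bias and no type I error inflation is claimed. The plan should be changed, but the trial's validity under randomisation is not in question here.

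**What to change.** In sections 10.1 and 12:

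1. Prespecify log baseline seizure rate as a covariate, whether or not it differs between the arms.
2. Make the primary comparison robust to the skewed score, by one of two routes:
   - regress log(follow-up rate plus a fixed constant) on treatment and log baseline rate, with robust standard errors, and report 100 × (1 - rate ratio) with its 95% CI; or
   - use a rank ANCOVA of the percentage reduction, which keeps the stated outcome.
3. Summarise the per-patient percentage by median and quartiles.
4. Before outcome data are analysed, re-express the 10-point margin and the section 11 inputs on the chosen scale, or state that they apply only to a supportive mean-percentage analysis.
5. Fix the constant for zero counts, and state how a zero baseline within the valid diary days is handled. The percentage, and so its rank, is undefined there.

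The cost is an amendment while enrolment, begun in December 2022, may be under way. No new data are needed, because diary counts and valid days are already collected. On the log route the effect measure changes to a relative reduction against control, and a margin on that scale has still to be justified. The rank route avoids the first change but gives no direct effect size in percentage points.

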**10.2 Secondary outcomes**

The secondary efficacy outcomes include the percentage decrease in the average duration of seizures after surgery compared with before, improvement in the severity of epilepsy after surgery, frequency of epileptiform discharge by 24h video EEG, evaluation of postoperative quality of life, improvement in migraine in patients with migraine complications, headache impact test, incidence rate of adverse events, cardiac ultrasound index, and some laboratory indicators.

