7.Participants with existing severe systemic diseases, such as digestive, circulatory, respiratory, liver, urinary, musculoskeletal, immune, or genetic metabolic diseases, whom researchers judge might be a potential impact on the results of the trial.

8.Participants who received head surgery or neuromodulation.

9.Participants under consideration for seizure-related surgery or any surgery involving general anesthesia, or who were already under general anesthesia four weeks before the screening period.

10. Participants who receive vaccinations during the screening period or four weeks before.

11. Participants preparing for pregnancy or breastfeeding during the trial period or three months after the study.

12. Patients who are participating in other interventional clinical studies during the trial.

13.Participants who are planning to travel or live abroad during the study period and cannot be followed-up.

14.Participants deemed inappropriate by the researchers for other reasons (need for detailed recording).

**Table 1. Schedule of enrolment, intervention and assessment according to the Standard Protocol Items: Recommendations for Interventional Trials (SPIRIT) statement**

|  | **Study Period** | | | | | | | | |
| --- | --- | --- | --- | --- | --- | --- | --- | --- | --- |
|  | **Screening** | **Enrolment** | **Allocation** | **Intra-operation** | **Post-operation** | | | | **Close - out** |
| **Time Point*** | **-7 to -2** | **-1** | **-1** | **0** | **4** | **12** | **24** | **48** |  |
|  | | | | | | | | | |
| **Screening** | | | | | | | | | |
| **General information** | **X** |  |  |  |  |  |  |  |  |
| **Eligibility screening** | **X** |  |  |  |  |  |  |  |  |
| **Epilepsy diary** | **X** |  |  |  |  |  |  |  |  |
| **Enrolment** | | | | | | | | | |
| **Informed consent** |  | **X** |  |  |  |  |  |  |  |
| **Allocation** |  |  | **X** |  |  |  |  |  |  |
| **Interventions** | | | | | | | | | |
| **PFO closure** |  |  |  | **X** |  |  |  |  |  |
| **Clopidogrel 75mg** |  |  |  |  | **X** | **X** |  |  |  |
| **Aspirin 100mg** |  |  |  |  | **X** | **X** | **X** |  |  |
| **Assessment** | | | | | | | | | |
| **Seizure frequency** |  |  |  |  | **X** | **X** | **X** | **X** | **X** |
| **Seizure duration** |  |  |  |  | **X** | **X** | **X** | **X** | **X** |
| **Seizure severity** |  |  |  |  | **X** | **X** | **X** | **X** | **X** |
| **Life quality** |  |  |  |  |  | **X** |  | **X** | **X** |

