| **Headache score** |  |  |  |  |  | **X** |  | **X** | **X** |
| **Adverse events** |  |  |  |  | **X** | **X** | **X** | **X** | **X** |

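### Two secondary outcomes worded as improvement (epilepsy severity, migraine) have no specified baseline score, and the video EEG outcome has no scheduled follow-up recording

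*Protocol*

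**What the plan says.** Protocol Section 10.2 names, among the secondary efficacy outcomes, "improvement in the severity of epilepsy after surgery, frequency of epileptiform discharge by 24h video EEG, evaluation of postoperative quality of life". The same sentence continues with "improvement in migraine in patients with migraine complications, headache impact test". The list also appears in Section 10.1, and the Protocol Summary names severity, EEG discharges and quality of life as well.

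Table 1 (in Section 5.2) has nine columns: screening, enrolment, allocation, intra-operation, weeks 4, 12, 24 and 48, and close-out. Its relevant rows read:

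- "Seizure severity | | | | | X | X | X | X | X"
- "Life quality | | | | | | X | | X | X"
- "Headache score | | | | | | X | | X | X"

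Table 1 has no EEG row. The only dated video EEG is in inclusion criterion 5, where the screening seizure must be "confirmed by a 24-hour video electroencephalogram (EEG) immediately after the seizure".

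Section 6.2 lists the baseline tests. They include medical history, a neurology evaluation, ECG, echocardiography, imaging and blood tests, but no severity scale, quality-of-life instrument, headache score or EEG. Section 5.1 places the recording of severity and quality of life in the follow-up period.

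**The concern.** An outcome worded as improvement needs a value from before treatment. If the schedule does not collect one, sites have no instruction to measure it, and the analysis has nothing defined to subtract or adjust for. An outcome read from a 24-hour video EEG likewise needs a dated recording after treatment.

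Timing matters more here because the trial is open-label. Severity, headache and quality-of-life ratings can be influenced by knowing the allocation, so a baseline taken or reconstructed after allocation is not a sound substitute. A statistical analysis plan can choose the model, but it cannot supply a measurement that was never made. The stake is the interpretability and precision of several secondary outcomes. The primary outcome is not affected by this point.

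**Working it through.** The protocol gives no figure to reproduce here, so the check sets the schedule against the outcome list.

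**Step 1. Marks in Table 1, column by column.**

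| Row | Before allocation | After treatment starts |
|---|---|---|
| Seizure severity | none | weeks 4, 12, 24, 48, close-out |
| Quality of life | none | weeks 12, 48, close-out |
| Headache score | none | weeks 12, 48, close-out |
| Seizure frequency (comparison) | none | weeks 4, 12, 24, 48, close-out |
| Epilepsy diary (comparison) | screening | none |
| Video EEG | no row | no row |

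**Step 2. Is a baseline supplied elsewhere?** For seizure frequency it is. Section 10.1 says that the preoperative frequency comes from valid seizure diaries, and Table 1 marks the diary at screening. No comparable rule exists for severity or migraine. The neurology evaluation and medical history in Section 6.2 are not tied to any score, and Section 5.2 only says that neurologists assess the epilepsy log in the eCRF.

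**Step 3. What each outcome needs.**

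- Severity, worded as improvement: follow-up values are scheduled; the baseline is not specified.
- Migraine, worded as improvement among patients with migraine: headache scores are scheduled at weeks 12 and 48 and close-out; no baseline score is specified.
- Epileptiform discharges on 24-hour video EEG, worded as a frequency: a screening recording is required by inclusion criterion 5; no follow-up recording is dated anywhere.
- Quality of life, worded as a postoperative evaluation, and the headache impact test, named without a change definition: both can be compared between arms from weeks 12 and 48.

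**Step 4. What a missing baseline costs where post-treatment values suffice.** With equal variances before and after treatment and baseline to follow-up correlation ρ, covariance adjustment multiplies the variance of the treatment difference by 1 − ρ², relative to comparing follow-up values alone.

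- ρ = 0.5: 1 − 0.25 = 0.75, a reduction of 25%.
- ρ = 0.7: 1 − 0.49 = 0.51, a reduction of 49%.

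The protocol gives no correlation. The range 0.5 to 0.7 is an assumption, and the result is illustrative only.

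**The case against.** The strongest reply is that a blank cell in Table 1 does not prove that nothing will be measured. The table is clearly not exhaustive. It omits the screening video EEG of inclusion criterion 5, the baseline ECG, imaging and blood tests of Section 6.2, and the 6-month TEE of Section 6.3. Seizure frequency has no baseline mark either, yet its baseline is defined. The assessment block may simply list postoperative visits, and the diary, the neurology evaluation or the medical history might yield a baseline for severity or migraine.

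This reply stands in part. It rules out several stronger readings that a reader might infer:

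- **That these outcomes cannot be computed at all.** Quality of life and the headache impact test can be compared on post-treatment values. For severity and migraine, the baseline is unspecified rather than shown to be impossible.
- **That the EEG outcome will be entirely missing after baseline.** Section 10.2 names the recording as an outcome measure, so some follow-up EEG is evidently intended. What the protocol lacks is its time point.
- **That a screening EEG taken just after a seizure will make both arms appear to improve.** The protocol does not define the EEG outcome as a change from that recording and gives no data on the matter. A shift common to both arms would not by itself bias the comparison between them.

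The reply does not close the gap. None of the possible sources names a score, and neither Table 1 nor the text dates a follow-up EEG.

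**Conclusion.** The point holds as a mismatch between the outcome list and the assessment schedule. Two outcomes worded as improvement, severity and migraine, have no specified pre-allocation score. One outcome, discharge frequency on video EEG, has no scheduled post-treatment recording. Quality of life and the headache impact test remain reportable and lose only change scores and baseline adjustment. The 25% to 49% variance reduction indicates what that adjustment could be worth under the assumed correlations; it is not an estimate for this trial.

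The conclusion rests on reading Table 1, Section 5.1 and Section 6.2 as the full instruction to sites. If a site manual or the case report form already collects these scores before allocation and dates the EEG, the remedy is only to bring the protocol into line. The issue concerns secondary outcomes but should be corrected promptly, because a baseline not taken before allocation in an open-label trial cannot be soundly recovered.

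**What to change.** Reconcile Section 10.2 with Table 1 and Section 6.2:

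1. Add marks in Table 1 for seizure severity, headache score and quality of life at screening or enrolment. State that they are completed before allocation, since enrolment and allocation both fall at week −1. List the same assessments in Section 6.2.
2. Add a Table 1 row for the 24-hour video EEG already named as an outcome, showing the screening recording and a follow-up time point that is the same in both arms.
3. For participants already randomised, document which baseline values exist and how each was obtained.

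The analysis model can stay with the statistical analysis plan. The cost is a schedule amendment and a few minutes of questionnaires per participant before randomisation. The follow-up EEG adds no new outcome, since the protocol already names it. The main drawback is that participants randomised before the amendment may lack baseline values, so change and baseline-adjusted results could be incomplete for them.
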